### Unaccompanied group

In the unaccompanied version, the subject works independently throughout the programme.

A chat function with a psychotherapist in training is available in the “classroom”, which can be used to clarify questions for improved understanding. There is no content-based discussion about the chat. The psychologist was also trained here.

### Control group

At the end of the follow-up period, subjects in the control group will receive free access to the online intervention programme. They are free to choose the version of the programme (accompanied or unaccompanied) they prefer. The control group received isolated, nonspecific mood-stabilizing activities such as body scan instructions, guided abdominal breathing and guided imagery. Subjects in the control group will not receive treatment or support from the researchers. However, they are free to seek any other help including pharmacological and psychological treatments. All concurrently used treatments will be measured repeatedly through self-report. Subjects in the control group will have access to the intervention after the last follow-up assessment, 12 weeks after the baseline assessment. The control group could not participate in “Selfapy” within 24 weeks. Duplicate registrations are prevented by comparing email addresses. Moreover, in the interviews, subjects are asked whether they registered more than once.

### Responses to crises and suicidality

A physical overuse can be excluded. The online survey at the time of measurement T1, T3 and T4 of the survey will take about 60 min (Table 2). The processing time for T2 is about 30 min. A general side effect of the interventions could possibly be a lack of treatment success. The most severe adverse event that could happen is acute suicidality. Suicidality is monitored using the BDI-II (after 6, 12 and 24 weeks) and the HRSD-24 (after 12 and 24 weeks). In case of a score of 3 (suicidal thoughts or behaviour) on item 3 on the HRSD-24 or in case of a score of 2 (suicidal thoughts or wishes) on item 9 of the BDI-II, discontinuation will be initiated. Each rater has an emergency plan, and the respective participant will be shifted to inpatient or outpatient psychotherapy.

**Table 2 Tab2:** Assessment tools utilized throughout the programme

Assessment timeframe	Assessment instrument
Pre (T1)	Self-assessment—questionnaires: BDI-II; QIDS-SR16; BAI; WHOQOL-BREF; SWOP-K9; WAI-SR; APOI; SASS; Bado
	Assessment by a therapist – Questionnaires: MINI; HRSD-24
During (T2)	Self-assessment—questionnaires: BDI-II; QIDS-SR16; BAI; WAI-SR; APOI
Post (T3)	Self-assessment—questionnaires: BDI-II; QIDS-SR16; BAI; WHOQOL-BREF; SWOP-K9; WAI-SR; APOI; SASS; Bado Assessment by a therapist—questionnaire: HRSD-24
Follow-up (T4)	Self-assessment—questionnaires: BDI-II; QIDS-SR16; WHOQOL-BREF; Bado Assessment by a therapist—questionnaire: HRSD-24

*Abbreviations*: *MINI*, Mini International Neuropsychiatric Interview; *BDI-II*, Beck Depression Inventory-II; *QIDS-SR16*, Quick Inventory of Depressive Symptomatology; *BAI*, Beck Anxiety Inventory; *WHOQOL-BREF*, WHO Quality of Life-BREF; *SWOP-K9*, Self-Efficacy, Optimism, and Pessimism Scale; *WAI-SR*, Working Alliance Inventory - Short Revised; *APOI*, Attitudes towards Psychological Online Interventions Questionnaire; *Bado*, basic documentation; *HRSD-24*, Hamilton Depression Scale; *SASS*, Social Activity Self-Assessment Scale

Subjects are allowed to attend ongoing psychotherapy. This reflects everyday treatment and ensures high external validity. Furthermore, it limits potential negative consequences due to the lack of treatment success, as additional treatment can be accessed, when needed. All potentially relevant factors for treatment outcome are taken into account for the statistical evaluation.

Voluntary termination was handled according to the study programme. Researchers will go beyond the protocol to contact dropped-out participants and try to continue the collection of data.

In case of harm induced by the trial, even though this is unlikely as depicted above, there is insurance coverage for the study participants provided by Selfapy’s public liability insurance GmbH. There are no guidelines for stopping the study. The study design was approved by the ethics committee of the medical faculty of the Charité University Medicine Berlin.

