### Inclusion and exclusion criteria

To clarify the inclusion and exclusion criteria, interviews will be conducted with all subjects via telephone (MINI, HRSD-24).

All MINI and HRSD-24 interviews will be conducted by the same two trained interviewers, who are a psychologist and a medical student. The training of the interviewers was delivered at the Charité Department of Psychiatry and Psychotherapy. Within this training, an opportunity to practise with depressive patients was provided, followed by a discussion regarding the ratings guided by a psychiatric consultant.

To be eligible, participants must (1) be between 18 and 65 years old, (2) have sufficient German language skills, (3) have uninterrupted access to the Internet, (4) score 12 or higher on the BDI-II, (5) provide their electronic data with the “declaration of consent” and (6) have a major diagnosis of a depressive episode or dysthymia (ICD-10: F32; F33; F34) (according to the MINI).

Subjects were excluded if they met one of the following criteria: (1) diagnosis of a bipolar disorder; (2) currently present psychotic symptoms or a diagnosis of an acute schizophrenic disorder (ICD-10: F2x; F31; F32.3; F33.3), acute substance dependence or withdrawal syndrome (ICD-10:F1x.2; F1x.3); or (3) they are currently experiencing or have experienced suicide ideations (operationalized via HRSD-24—subjects are excluded if they have a score of 3 or above on suicidality items) in the past.

A comorbid diagnosis other than depression is not an exclusion criterion, as the aim was to reflect routine care as realistically as possible. However, an active substance dependency is an exclusion criterion, as psychotherapy is not indicated during an active substance dependency as this limits any intervention (e.g. intoxication, concentration deficit, withdrawal symptoms). In addition, acute addiction could distort the effectiveness of the programme in patients with depression. Other primary psychiatric disorders are excluded as including these patients will reduce the internal and external validity of our trial, which targets the effects of the programme for patients with depressive disorder.

Subjects who do not meet our inclusion criteria due to the severity of illness are encouraged to seek professional help.

Adequate language skills are determined during the initial diagnosis by the MINI and HRSD-24. Our inclusion criteria were critically discussed in the study board.

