### Randomization and blinding

Subjects who meet the inclusion criteria will be randomly allocated to one of the three groups: (a) immediate access to the unaccompanied depression course of “Selfapy”, (b) immediate access to the accompanied depression course of “Selfapy” or (c) access to “Selfapy” after a delay of 24 weeks (control group).

Block randomization is performed by an independent researcher using a random number assignment plan for this list, which was created by a computer-controlled random number generator. These numbers are assigned blindly, i.e. subjects and researchers have no knowledge of which group a patient was allocated to. The subjects are randomly assigned to one of the three groups in a ratio of 2:2:1. The subjects will be informed by email about the result of the allocation process. Subjects in one of the intervention groups received an email with a link and their respective access code to register and be able to start the intervention immediately. Subjects in the control group who also received an email with a link that leads the subject to the assessment material will be informed by email about the result of the random assignment. Therefore, participants enrolled themselves in the study programme. Diagnostic interviewers are blind to the assigned group of subjects. An illustration of the patient flow can be found in Fig. 1.

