**Fig. 1 Fig1:**
[figure not shown]
“Selfapy” programme flowchart

After successfully completing the MINI and HSDR-24, the unblinding of the researchers will be possible in the case of acute suicidality and before the study programme will be terminated for the respective participant.

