### Planned statistical analysis

The recorded data of the different measurement times (T1, T2, T3 and T4) for both intervention groups and the control group are analysed. The treatment results of all subjects (pre-post difference) are analysed using intention-to-treat (ITT) analyses.

The primary endpoint is the decrease in depressive symptoms in the BDI-II (Delta BDI-II) between study entrance (T1) and the end of the intervention (T3). A one-way ANOVA (within factor “group”) is performed to analyse the differences in the decrease of depressive symptoms between the intervention groups. A Bonferroni correction for multiple testing is applied to examine the expected group differences. This correction is carried out using the formula *α*/*n* (with alpha level *α* = 0.05 and *n* = number of tests) in order to lower the level of significance, make fewer results significant and thus the number of false-positive results reduce.

In an exploratory analysis, the basic effectiveness of the intervention compared to the control condition is examined (accompanied and unaccompanied group vs. control group) in order to counter the high drop-out rate.

In addition, the mean values including confidence intervals (95%) are recorded. The data are aggregated in the form of mean values and standard deviations. No interim analyses are planned.

To check the data obtained from the measuring instruments for normal distribution, the Kolmogorov-Smirnov test is calculated at the beginning. For this purpose, the mean values and standard deviations of each variable, as well as the Kolmogorov-Smirnov *Z*-value, are calculated, and the asymptotic significance (two-sided) is determined. Values below 0.05 indicate a violation of the normal distribution.

The intermediate measurements are analysed with regard to continuous outcome measures using repeated-measure ANOVAs. Independent *t* tests and *χ*^2^ tests are used to estimate the intergroup differences in sample characteristics prior to treatment.

Missing values in the data are replaced by multiple imputations, as well as “last-observation-carried-forward” (LOCF), “baseline-observation-carried-forward” (BOCF) and a “reference-based multiple imputation” method (“jump-to-reference” approach) to replace the missing values.

Effect size calculations to measure the therapeutic success (before and after the intervention) are carried out by dividing the difference between the respective group mean values by their pooled standard deviation.

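### A subject scoring 2 on BDI-II item 9 at T1 can be randomised, although the same answer alone triggers discontinuation from week 6

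*Protocol article*

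**What the plan says.** Entry (protocol article, Inclusion and exclusion criteria). Current or past suicidal ideation is an exclusion, and the section gives one operational rule for it, based on the HRSD-24: "subjects are excluded if they have a score of 3 or above on suicidality items". The BDI-II enters eligibility only as a total; subjects must "score 12 or higher on the BDI-II". No item-level BDI-II rule is given.

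Allocation (Randomization and blinding). "Subjects who meet the inclusion criteria will be randomly allocated to one of the three groups".

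On study (Responses to crises and suicidality). The schedule reads "Suicidality is monitored using the BDI-II (after 6, 12 and 24 weeks) and the HRSD-24 (after 12 and 24 weeks"). Two triggers are joined by *or*: a score of 3 on HRSD-24 item 3, or "a score of 2 (suicidal thoughts or wishes) on item 9 of the BDI-II, discontinuation will be initiated". The emergency plan and a move to inpatient or outpatient psychotherapy follow.

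Instruments (Table 2). The BDI-II is completed at T1, T2, T3 and T4. The HRSD-24 is done at T1, T3 and T4, but not at T2.

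**The concern.** The HRSD-24 threshold is 3 both at entry and on study. The BDI-II item 9 threshold exists only on study. The protocol labels an item 9 score of 2 as suicidal thoughts or wishes, which is the kind of state the entry exclusion is meant to cover, yet the operational rule for that exclusion does not use it.

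What is at stake is safety. The protocol names acute suicidality as the most severe adverse event that could occur. Followed as written, an answer that leads to discontinuation and referral at T2, T3 or T4 leads to nothing at T1, and the subject may be allocated to an arm with little or no professional contact. A subject whose answer simply stays the same would then be discontinued at week 6 without having worsened.

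**Working it through.** The plan gives no figure to reproduce, so the check sets the rules side by side and follows one case through them.

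| Time point | BDI-II done | HRSD-24 done | Stated suicidality rule |
|---|---|---|---|
| T1 | yes | yes | HRSD-24 suicidality 3 or above: exclude. No item 9 rule |
| T2, week 6 | yes | no | Item 9 = 2: discontinue |
| T3, week 12 | yes | yes | HRSD-24 item 3 = 3, or item 9 = 2: discontinue |
| T4, week 24 | yes | yes | HRSD-24 item 3 = 3, or item 9 = 2: discontinue |

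**Worked case.** Item 9 = 2, HRSD-24 suicidality between 0 and 2, BDI-II total of at least 12, all other criteria met.

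1. T1: no written exclusion applies, so the subject is randomised.
2. T2, same answer: item 9 = 2, so discontinuation is initiated.
3. T3 and T4, same answers: item 9 alone suffices even though an interview is done at the same visit, because the two triggers are alternatives.

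**Is item 9 known before allocation?** Yes. The BDI-II total is an inclusion criterion, and only subjects who meet the criteria are allocated, so the questionnaire must be scored first.

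**Does the entry cut-off screen such subjects out?** No. With item 9 = 2, the remaining items need only 12 − 2 = 10 points.

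**Length of the gap.** The first listed item 9 check is at week 6 of a 12-week programme: 6/12, or half of it.

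**Contact during the gap.** The accompanied arm (160 planned) has weekly calls. The unaccompanied arm (160) has a chat for clarifying questions, and the control arm (80) has no treatment or support from the researchers. Those two arms together are 160 + 80 = 240 of 400, or 60%.

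**Number affected.** The share with item 9 of 2 or more and HRSD-24 suicidality below 3 at T1 is not given, so no count can be computed. As a scale, 1% of 400 is 4 subjects.

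**The case against.** The strongest defence is that the asymmetry is deliberate. Every subject has a live interview at entry (MINI and HRSD-24) by trained interviewers, whereas T2 has no interview, so a cautious self-report trigger is the only one available there. T3 falls at the end of the programme and T4 later, so by then no programme remains to be stopped. This explains why item 9 is needed at T2. It does not explain why item 9 still counts alone at T3 and T4, where an HRSD-24 interview is also done; the protocol does not let the interview override the self-report there. The MINI is added at T1 only, but the suicidality exclusion is tied to the HRSD-24, not to the MINI.

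Second, the trigger sentence carries no time limit of its own; the restriction to week 6 onwards comes from the monitoring sentence before it. If the trigger did cover T1, it would still not be an eligibility rule, and the subject would be randomised and then discontinued at once.

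Third, an interviewer could exclude such a subject on the general wording about suicidal ideation. That is possible, but the stated operational definition does not require it.

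Fourth, a condensed article may leave screening procedures to the full protocol or the emergency plan. Here, however, both the entry rule and the discontinuation rule are stated in the article, and they do not match.

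Two parts of the defence stand. The affected group is limited to subjects whose self-report and interview disagree, and its size is unknown. The weekly calls, and staff training that covered risks, also reduce the gap for the accompanied arm, though not for the other two.

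**Conclusion.** The concern holds. The entry and discontinuation rules for suicidality are inconsistent: the BDI-II half of the on-study rule is missing at entry, although the data are in hand before allocation. The consequence is up to 6 weeks without a stated action on an answer that the plan otherwise treats as grounds for discontinuation and referral. The number affected cannot be derived from the documents.

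This rests on two readings: that the monitoring schedule governs when the item 9 trigger is applied, and that a score of 2 means 2 or above. No bias in the primary outcome is claimed. The point should be corrected as an inexpensive safety improvement.

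**What to change.** 1. Apply BDI-II item 9 of 2 or above at T1, either as an added exclusion in Inclusion and exclusion criteria or as a trigger for the crisis procedure before randomisation. The investigators should choose one and state it. This is the change that matters.
2. As a clarification, write the on-study thresholds in Responses to crises and suicidality as 3 or above for HRSD-24 item 3 and 2 or above for BDI-II item 9, matching the entry wording.
3. As a further clarification, state that safety discontinuation in any arm ends programme use only, and that T3 and T4 assessments are still sought and used. This agrees with what the article already says: in acute suicidality "the study programme will be terminated for the respective participant", researchers will "contact dropped-out participants and try to continue the collection of data", and treatment results "are analysed using intention-to-treat (ITT) analyses".

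**Cost.** A short amendment of two sections and no new assessment. A few otherwise eligible subjects would be excluded or referred at entry. On the last count given in Trial status (298 recruited on 28 May 2020), the new entry rule would reach at most 400 − 298 = 102 further subjects, and fewer if recruitment has since advanced. For those already randomised, T1 item 9 can be tabulated by arm from data already held, which would also show how many were affected.

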### Ethics and data protection

It is ensured that data can be not associated with personal data of the participant, e.g. name. In case of subsequent withdrawal from consent, the respective participant is identified via a code-word. Data is saved on CDs, which are stored in a safe and only accessible to a small number of people involved in the research project; data will be archived for 10 years after completion of the trial and then deleted.

### Assessments

Assessments will be made at four distinct points in time. Baseline (T1, study entrance), 6 weeks after baseline (T2), 3 months after baseline (T3, end of the programme) and 12 weeks after the completion of the programme (T4, follow-up). All other questionnaires are completed by the subjects (self-rating).

### Outcome measures

#### Primary outcome measure

The primary outcome measure is the change in the self-assessment of depressive symptoms after the completion of the programme using the BDI-II on all assessment points.

#### Secondary outcome measures

Changes in depressive symptoms will be additionally assessed at baseline (T1) and post (T3) after 12 weeks as well as at follow-up (T4) using observer-rated inventories HRSD-24 and the QIDS [25].

Furthermore, changes in the self-assessment of anxiety-related symptoms will be analysed using the BAI [26]. Changes in self-esteem will be evaluated using the SWOP-K9 [27]. Similarly, the SASS [28] questionnaire will be utilized to record the levels of social activation. The WHOQOL-BREF [29] will be used to assess the impact of the programme on physical changes and life satisfaction. The APOI captures attitudes towards online interventions [30].

The WAI [31] is an employment inventory for the collection of therapeutic alliances and is used to evaluate work alliances. The ACSA is a self-anchoring rating scale for subjective well-being that was originally developed as a simple method to measure the quality of life consecutively in the patient-physician relationship [32]. The Bado sheet is used to assess the impact of the programme on subjects’ use of the healthcare system, including contact with healthcare providers, the number of therapy sessions and the amount of contact with psychotherapists and psychiatrists.

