**Methods:**

A sample of 400 subjects that have a mild to severe depressive episode (Becks Depression Inventory - II and Hamilton Depression Scale) will be used. Subjects are randomly assigned to immediate access to an unaccompanied course (no support from psychologist via weekly phone calls), immediate access to an accompanied course (support from a psychologist via weekly phone calls) or a waiting list control group (access to the intervention after 24 weeks). The intervention will last for a period of 12 weeks. Depressive symptoms as a primary parameter, as well as various secondary parameters, such as life satisfaction, therapeutic relationships, social activation, self-esteem, attitudes towards Internet interventions and drop-out rates, are recorded at four different points in time: at baseline (T1), 6 weeks after the start of the intervention (T2), 12 weeks after the start of the intervention (T3) and 3 months after completion of the treatment follow-up (T4).

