#### Secondary hypotheses

The drop-out rate is expected to be higher for the unaccompanied group than for the accompanied group.The strength of the therapeutic relationship will be significantly higher in the accompanied group than in the unaccompanied group.Positive attitudes towards Internet interventions will increase for the accompanied group as well as for the unaccompanied group when compared with reported attitudes at baseline. Increased scores in positive attitudes towards Internet interventions will be significantly higher for the accompanied group than for the unaccompanied group.Quality of life, social activation and self-esteem scores will increase significantly over the duration of the 3-month programme compared to scores taken at baseline and compared to scores in the control group. The increase in these parameters will be significantly higher for the accompanied group than for the unaccompanied group.

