**Target selection**		
First insights	In this module, the user is brought closer to the connection between thinking, feeling and acting. Based on this triangular connection, our course concept is explained to him/her.	Your personal triangles
Resources	Power sources are explained and gathered. Different methods are introduced to assist users in collecting power sources. Behavioural activation is prepared.	Evaluation daily protocol; power source images; treasure chest; resource walk
Behavioural activation	How to actively plan power sources during the day is explained.	Activity plan
Automatic thoughts	Automatic thoughts and thinking patterns are addressed.	Automatic thoughts; core beliefs
Realistic thoughts	The content of this module focuses on thinking about reality and thinking realistically.	Think realistically
Self-esteem	A positive self-concept is important for overcoming problems. The user learns how the concepts of self-confidence and self-acceptance can help to develop a positive self-image.	Positive self-image
Self-efficacy	The user is made aware of recent successes. This will enable him or her to better allocate his or her power reserves and increase confidence in his or her abilities.	“Your personal achievements—be proud of yourself”
Solve problem	Training to perceive a specific problem, gather potential responses in a problematic situation and develop the competence to implement a particular course of action to solve this problem optimally is introduced.	Problem-solving training
Mindfulness + excursus: pleasure training	In this module, mindfulness is the focus. A mindful approach is cultivated to improve stress management.	Mental note; mindfulness in everyday life; sitting meditation; body scan; your enjoyment moments
Social environment + stigma + social support	The focus of this module is on the environment and the social environment of the user. How social support can help to deal appropriately and successfully with stress is clarified.	“Difficult communication—your backing”
Relapse cases	Finally, a tool is introduced to help the user recognize when stress increases and becomes too much and how to handle it when the stress cannot be avoided.	Risk situations; early warning symptoms; first aid plan; relapse protocol

Subjects are advised to spend at least 15 to 20 min a day on the programme. If the modules are not processed for 3 weeks (recorded via login), this will be counted as the subjects drop out.

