## Abbreviations

ACSA: Anamnestic Comparative Self-Assessment
APOI: Attitudes towards Psychological Online Interventions Questionnaire
Bado: Basic documentation
BAI: Beck Anxiety Inventory
BDI-II: Beck Depression Inventory-II
CBT: Cognitive behaviour therapy
HRSD-24: Hamilton Depression Scale
CI: Confidence interval
iCBT: Internet-delivered cognitive behaviour therapy
MINI: Mini International Neuropsychiatric Interview
RCT: Randomized controlled trial
SASS: Social Activity Self-Assessment Scale
SMD: Standardized mean difference
SWOP-K9: Self-Efficacy, Optimism and Pessimism Scale
QIDS-SR: Quick Inventory of Depressive Symptomatology Self-Report
WAI: Working Alliance Inventory
WHOQOL-BREF: WHO Quality of Life-BREF

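### The self-esteem outcome is assigned to a scale that the protocol itself names as measuring self-efficacy, optimism and pessimism

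*Protocol article*

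**What the plan says.** The Abstract lists self-esteem among the secondary parameters: "life satisfaction, therapeutic relationships, social activation, self-esteem, attitudes towards Internet interventions and drop-out rates". The Discussion names it again as one of the further parameters to be investigated.

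The section on secondary hypotheses turns it into a prediction: "Quality of life, social activation and self-esteem scores will increase significantly over the duration of the 3-month programme". The comparison there is with baseline and with the control group. The next sentence adds the contrast between the two versions of the programme: "The increase in these parameters will be significantly higher for the accompanied group than for the unaccompanied group".

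The section on secondary outcome measures names the instrument: "Changes in self-esteem will be evaluated using the SWOP-K9". The footnote to Table 2 gives that instrument's full name as "Self-Efficacy, Optimism, and Pessimism Scale". The abbreviation list agrees: "SWOP-K9: Self-Efficacy, Optimism and Pessimism Scale".

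**The concern.** The outcome is labelled with one construct, and the instrument is named for three others. If the plan is followed literally, any difference on the SWOP-K9 goes into the report as a change in self-esteem, although by the document's own naming the scale addresses self-efficacy, optimism and pessimism.

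The label matters for two reasons. Self-esteem appears in the abstract, the hypotheses and the discussion, so it is likely to be carried into the results as a finding in its own right. The programme also contains a module called self-esteem, so a mislabelled positive result could be read as evidence that this module achieves its aim.

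The predicted direction needs attention too. The hypothesis speaks only of scores increasing. For a construct such as pessimism, improvement would ordinarily be a decrease, unless that part of the scale is reverse-scored. The article does not say how it is scored.

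**Working it through.** No arithmetic applies to the main point. It depends on no effect size, alpha level or drop-out figure. The check is to follow the construct and the instrument through the document and see whether they meet.

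1. **Where the construct appears.** Self-esteem is named in the Abstract, the secondary hypotheses and the Discussion. The hypothesis carries three comparisons: with baseline, with control, and accompanied with unaccompanied.

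2. **Which instrument is assigned.** The section on secondary outcome measures assigns one, the SWOP-K9.

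3. **What that instrument is said to measure.** Both expansions of the name list self-efficacy, optimism and pessimism. Self-esteem is not among them.

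4. **Whether another instrument fills the gap.** The self-report battery at T1 and T3 in Table 2 is "BDI-II; QIDS-SR16; BAI; WHOQOL-BREF; SWOP-K9; WAI-SR; APOI; SASS; Bado". From the outcome sections and the names given, the others are tied as follows:

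| Instrument | Construct tied to it in the article |
|---|---|
| BDI-II, QIDS-SR16 | depressive symptoms |
| BAI | anxiety |
| WHOQOL-BREF | quality of life, life satisfaction and physical changes |
| WAI-SR | therapeutic alliance |
| APOI | attitudes to online interventions |
| SASS | social activation |
| Bado | healthcare use |

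   The interviewer-administered tools (MINI, HRSD-24) cover diagnosis and depression. The ACSA, described in the outcome section, covers subjective well-being. None is named or described as a self-esteem measure.

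5. **Whether a proxy is argued.** No sentence says that the SWOP-K9 stands in for self-esteem, or why it might.

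6. **Whether the article uses the terms interchangeably.** Table 1 has separate modules headed self-esteem and self-efficacy. Of the first it says: "The user learns how the concepts of self-confidence and self-acceptance can help to develop a positive self-image". The second is about noticing recent successes and gaining confidence in one's abilities. This suggests that the authors distinguish the two, but it is supporting evidence only, since module headings are not outcome definitions. Even if the two terms were taken as equivalent, optimism and pessimism would remain unaccounted for.

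7. **Whether a self-esteem scale could simply be added.** The Trial status section reports 298 participants recruited by 28 May 2020, out of a planned 400. That is 298 / 400 = 74.5% of the planned sample who would have no baseline value on a scale introduced after that date. Relabelling is therefore the workable route.

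**The case against.** The strongest reply is that the evidence is a name. The item content, scoring and validation of the SWOP-K9 lie in a cited source that is not part of the document. A reader might infer that the trial cannot test its self-esteem hypothesis, that it has no valid measure of it, or that self-esteem is never measured at all. The document does not support any of these. They are statements about validity, and Table 2 lists instruments without their items or domains. What can be shown is narrower: the label and the instrument's stated constructs disagree, and nothing in the text bridges them.

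A reader might also infer that pessimism is to be pooled with the other constructs into one score, which would make an increase uninterpretable. That does not stand either. The article mentions no total score and no subscales, and scoring is commonly left to the full protocol or the analysis plan. What survives is that a prediction of increase needs a direction for each construct once the constructs are named correctly.

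The mismatch may also be loose English; the article is imprecise elsewhere, for instance in describing the WAI as an employment inventory. That is plausible but unproven. It would explain how the label arose without removing the need to correct it, because the same label appears in the abstract, the hypotheses, the outcome section and the discussion.

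Finally, the consequence is limited: the instrument is openly named, so an attentive reader can see what was scored. That is correct and bears on the weight of the point. It does not make the stated pairing right. Nor is this a detail left to another document, since the article positively states a pairing that its own expansion of the name contradicts.

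**Conclusion.** The point holds as a mismatch between a declared secondary outcome and the stated constructs of the only instrument assigned to it. Its reach is one of the three constructs in one secondary hypothesis (the others being quality of life and social activation), with three comparisons that would carry the wrong label. The primary BDI-II endpoint, the sample size and data collection are unaffected.

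The conclusion assumes that the name given twice in the article describes the scale correctly. It makes no claim about the scale's items, subscales or validation. The remark on pessimism is conditional on how that part is scored. On that footing this should be corrected, because it changes what the trial may say it has shown, but it does not threaten the main result.

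**What to change.** Before any unblinded analysis:

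- Restate this part of the secondary hypothesis, and the outcome, as self-efficacy, optimism and pessimism measured by the SWOP-K9.
- Give the expected direction for each construct: self-efficacy and optimism to rise, pessimism to fall unless it is reverse-scored.
- Either drop the self-esteem claim wherever it is made (abstract, hypotheses, discussion), or keep it and say explicitly that the SWOP-K9 serves as a proxy, with the reason.
- Disclose the change when the results are published, as the end of the Discussion undertakes for any departure from the protocol.

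The cost is small but goes a little beyond editing. Renaming a hypothesis after recruitment has begun is a change to the stated hypotheses and has to be reported as one. The trial gives up, or qualifies, a claim about self-esteem. No new data are needed.
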